## Abstract

**Background:**

In social prescribing, link workers support individuals whose persistent health problems are exacerbated by loneliness by connecting them to community-based social activities. This approach is well established in the UK and is gaining attention in Australia. However, a major limitation of research to date has been a lack of theoretically informed and rigorous evaluations of social prescribing. We will address these points in this study, applying a social identity framework to examine the effects of group-based social prescribing (SP) activity compared to primary care treatment as usual (TAU).

**Methods:**

Ninety participants experiencing loneliness recruited from primary care services and community centres across five sites in Southeast Queensland will be assigned to one of two conditions (SP, TAU) and assessed at two timepoints (baseline, + 8 weeks). Individuals will be aged 18 years and over, have sufficient English language skills to provide consent, and at the time of recruitment they will not be experiencing acute symptoms or social issues that require urgent intervention. Primary outcomes are loneliness, mental well-being, and health service use (total number of GP, hospital, and allied health visits in the past 3 months). Secondary outcomes will assess social group processes, including number of important social groups, new group identification, multiple identity compatibility, and group-based support and emotion regulation.

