### Data collection

Data will be collected via survey by researchers either in-person or online when in-person data collection is not feasible. Participants will be allocated a study code so that no identifying information is collected with the surveys. The initial (T1) survey will be collected when participants first engage in social prescribing (i.e., when they begin to meet with the Link Worker, but are yet to attend a group or have only recently started attending a group activity). Participants will then be followed up 8-weeks later (T2). The number of group activities a participant joins during the 8-week period is up to the discretion of the participant and Link Worker, however, we expect that this will typically be just one new group. Surveys will be collected from the TAU participants across the same time interval of 8 weeks, and they will continue to receive primary care treatment as usual. Participants will be reimbursed with AUD $40 vouchers at T1 and T2. Non-identified service audit data will also be collected by researchers from the Link Workers to gain an overall sense of the total number of program referrals and the different referral pathways, as well as general demographic characteristics.

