### Measures

***The primary outcomes are loneliness, wellbeing, and health service use, and these will be assessed in both T1 and T2 surveys.***

*Loneliness* will be assessed via the 8-item brief UCLA Loneliness Scale [45] (e.g., ‘how often do you feel left out?’), in which responses are made on a 4-point scale (where 0 = *never*, 1 = *rarely*, 2 = *sometimes*, and 3 = *often*). Items are summed to produce a total score ranging from 0 to 24.

*Wellbeing* will be measured using the 14-item Warwick Edinburgh Mental Wellbeing Scale [46]. The items are positively worded and ask respondents how often they have experienced various psychological states over the past 2 weeks (e.g., ‘I’ve been feeling relaxed’) on a 5-point rating scale (where 1 = *none of the time* to 5 = *all of the time*). Scores are summed to produce a total score in the range from 14 to 70, with higher scores corresponding to a higher level of mental well-being. The WEMWBS is psychometrically robust in general populations, with excellent internal consistency (α = 0.91) and good test-retest reliability (*r* = .83) [46].

*Health Service Use* will be measured by the self-reported total number of visits that participants make to hospital, community mental health services, counsellor, psychologist, psychiatrist, social worker, GP (in person, over the phone, or via home visit) over the course of the study (adapted from the measure used in [47]). In addition, respondents will be asked to rate their current health on a single 5-point scale (where 1 = *very poor* to 5 = *very good)*.

Secondary outcomes are process measures by which the social prescribing intervention is expected to produce effects on the primary outcomes: group memberships and identities, new group identification, former and new group compatibility, and group-based psychosocial resources of social support and emotion regulation.

*Group memberships and identities* Participants will be asked to list up to six groups that they are members of and rate the importance of each on a 7-point scale (where 1 = *not important* to 7 = *very important).* From this, the number of important groups (i.e., those rated 5–7) will be derived (see [34], p. 350–351).

*New group membership and identification* Social identification with the (first) new group that the participant has joined through the social prescribing program will be measured by 4-items rated on a 5-point scale (where 1 = *strongly disagree* to 5 = *strongly agree* [48];).

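### Health service use, a primary outcome, is given two incompatible recall windows, one of which is undefined at baseline

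*Protocol article*

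**What the plan says.** The Abstract (Methods) names the outcome as "health service use (total number of GP, hospital, and allied health visits in the past 3 months". The Measures section instead counts self-reported visits made "over the course of the study (adapted from the measure used in [47".

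Measures also states: "The primary outcomes are loneliness, wellbeing, and health service use, and these will be assessed in both T1 and T2 surveys". The schedule is the same in both conditions. Data collection says of social prescribing (SP) participants "Participants will then be followed up 8-weeks later (T2", and of treatment-as-usual (TAU) participants "Surveys will be collected from the TAU participants across the same time interval of 8 weeks". For SP, T1 sits at the start of exposure: "The initial (T1) survey will be collected when participants first engage in social prescribing".

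The Power calculation section plans a 2 x 2 mixed analysis of variance for the primary outcomes. The Analysis section plans repeated-measures mixed models with timepoint and condition. Both use a value at T1 and a value at T2.

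The two places also list services differently. The Abstract gives GP, hospital and allied health. Measures gives hospital, community mental health, counsellor, psychologist, psychiatrist, social worker and GP.

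**The concern.** The two definitions differ in length (about 13 weeks against 8) and in where the window starts. Nothing in the article says which one governs. They cannot both be the primary outcome, and each has its own difficulty:

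- The course-of-study version has no value at T1, because no part of the study has yet elapsed for that participant. The model then has no baseline to work from.
- The 3-month version exists at both surveys, but follow-up is shorter than the window. Part of the T2 count is therefore fixed before the participant enters.

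A reader trying to honour both texts might use 3 months at T1 and 8 weeks at T2, which would produce a change from the definition alone. With the window left open in a non-randomised, retrospectively registered study, the choice could also be made after the data are seen.

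**Working it through.** **The plan's own figure.** The stated sample size reproduces. For two groups, f = 0.30 and alpha 0.05, the noncentral F calculation gives 90 as the smallest even total with power of at least 0.80 (power 0.804). It matches a two-group comparison at a single time. The window problem does not alter it.

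**Inputs.** Recall of 3 months (Abstract), taken as 13 weeks, or 12 on a looser convention. Follow-up of 8 weeks (Abstract; Data collection). TAU patients are selected for 12 or more practice visits a year (Design and participants). The documents give no visit rates or standard deviations, so any used below are assumptions.

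**1. Pre-baseline share of the T2 count under the 3-month window.** Recall minus follow-up:
- 13 - 8 = 5 weeks; 5/13 = 38%.
- With 12 weeks: 12 - 8 = 4; 4/12 = 33%.

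**2. Relative effect seen in the T2 count.** If the effect acts only after T1 with rate ratio RR, the ratio seen is (5 + 8 x RR)/13.
- RR = 0.70: (5 + 5.6)/13 = 0.82, so a 30% reduction appears as 0.30 x 8/13 = about 18%.
- RR = 0.50: (5 + 4)/13 = 0.69.
- With a 12-week window, 30% appears as 0.30 x 8/12 = 20%.

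**3. Condition-by-time contrast under the 3-month window.** Number weeks from T1.
- T1 count = weeks -13 to -5, plus weeks -5 to 0.
- T2 count = weeks -5 to 0, plus weeks 0 to 8.
- T2 minus T1 = weeks 0 to 8, minus weeks -13 to -5.

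The five shared weeks drop out, leaving two 8-week periods. The absolute effect is not diluted, but the reference period ends five weeks before baseline.

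A simulation agrees (assumed 0.25 visits a week, RR 0.5, overdispersed counts, 45 per arm). The standardised difference in change was 0.52 and power 0.69 under either window.

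**4. Mixed windows (3 months at T1, 8 weeks at T2).** With no real change, the T2 count is 8/13 = 62% of the T1 count, a fall of 38% in both arms. The absolute fall depends on the starting level:
- TAU at the selection threshold: 12 a year is 3 per 13 weeks, and 3 x 5/13 = 1.15 visits.
- SP at an assumed 1.5 per 13 weeks: 1.5 x 5/13 = 0.58 visits.
- Spurious difference in change: 1.15 - 0.58, about 0.6 visits. It is zero if the arms start level and grows with the gap between them.

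**The case against.** The strongest reply is that the harm is smaller than it looks. A reader might infer that a window reaching back before baseline dilutes the effect and costs power. For a comparison of T2 counts alone, d = 0.60 would shrink to 0.60 x 8/13 = 0.37 if variation between persons dominates, or to 0.60 x sqrt(8/13) = 0.47 with independent Poisson weeks. Power at 90 would then fall from 0.80 to about 0.41 or 0.60. The documents do not support this as the consequence. The hypothesis is improvement relative to TAU, and the planned models use both timepoints; in that contrast the shared weeks cancel. This objection stands, and the power loss should not be claimed.

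It is also fair that a 3-month item can be asked identically at both surveys, so the outcome is not unmeasurable. The mixed-window scheme is written nowhere; it is a risk left open by the text, not a stated plan.

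The service lists carry less weight. An abstract condenses, and allied health can plausibly cover counsellors, psychologists and social workers.

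A reader might also argue for a count model here. That choice is commonly settled in an analysis plan, and the case for it would rest on assumed visit rates, so it is no part of this point.

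A lenient reading takes the Measures phrase to mean only that the item is administered during the study. But the phrase attaches to the visits being counted, and the 3-month period does not appear in that section. None of these replies reconciles the two windows or supplies a baseline for the second.

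**Conclusion.** Wrong as written. One of three primary outcomes has two recall windows that cannot both hold, and the one in Measures is undefined at T1 although that section requires it there. This rests on the text alone.

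If the 3-month window governs, 33% to 38% of the T2 window precedes baseline. A true 30% reduction then reads as about 18% in the T2 count (20% if 3 months means 12 weeks), assuming the effect begins at T1. The condition-by-time contrast keeps its power if recall is accurate, but compares follow-up with weeks -13 to -5 and not with the 8 weeks before baseline, a contrast the article does not state. If the windows were mixed, counts would fall by about 38% with no real change, and by more visits in whichever arm starts higher. TAU's selection on frequent attendance makes unequal starting levels plausible, but the SP level is not given.

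**What to change.** State one recall window, no longer than the follow-up interval and identical at T1 and T2 (for example, *in the past 8 weeks*). Give one service list. Use both in the Abstract and in Measures.

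Registration was retrospective, so some participants may already have been surveyed. If so, do not change the window midway. Keep the window already used at both surveys and state it. If that is 3 months, report that the T2 count includes about 5 pre-baseline weeks and that the change contrast refers back to weeks -13 to -5.

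The cost is one reworded survey item, if surveying has not begun, and matching text in two sections. The downside of 8 weeks is that fewer visits are counted per person than over 3 months.

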**Discussion:**

This study will provide comprehensive data about the extent to which, and how, social prescribing to community-based group activities may help people to feel less lonely, more socially integrated, and healthy over the first 8 weeks. If effective, this social identity-informed model of social prescribing can be disseminated in communities across Australia.

**Trial registration:**

ANZCTR, Registered 8 June 2022 - Retrospectively registered, https://www.anzctr.org.au/ACTRN12622000801718.aspx

## Background

Loneliness is a painful emotional state that occurs when people feel that their social needs are not being met [1]. In Australia, surveys indicate that between 12 and 25% of people experience problematic levels of loneliness [2, 3]. It is recognised as a pressing public health issue worldwide [4, 5]. This is because loneliness has serious consequences for individual health and wellbeing, including an increased risk of coronary heart disease and stroke, depression, substance use, and premature death [6–9]. It is also associated with frequent attendance at general (medical) practice appointments and hospital emergency departments [10, 11]. It is important to understand and address loneliness in the context of increasing demand on health services and the need to reduce inappropriate health care usage.

Internationally, there is a growing interest in community-based preventative solutions to loneliness as part of a holistic approach to health care. Among these, social prescribing programs are gaining considerable traction [12]. The UK model of social prescribing is integrated into GP clinics and involves health professionals referring individuals to a link worker who supports them to join social activity groups delivered by diverse facilitators within the community [13–15]. Well-known models of social prescribing include ‘arts on prescription’ [16], ‘education on prescription’ [17], and ‘exercise on prescription’ [18]. A randomised controlled trial [19], single arm trials [20–23], and a systematic review [24] have found that social prescribing programs can be effective in reducing participants’ social isolation and loneliness, increasing community integration, and improving mood and mental well-being. However, there is a large variation in the models of social prescribing and the methods used to evaluate them [25], and this has led some researchers to be critical of the approach [26]. This has prompted calls for a theoretical framework to inform clients, link workers, and referring agents about how social prescribing can be implemented most effectively. The social identity approach has been identified as having particular value for social prescribing [27, 28].

The theoretical framework that forms the basis for the study builds upon social identity theory and self-categorisation theory [29, 30]. Together, these theories account for the role that social group memberships play in people’s lives via integration as part of their sense of self or identity. When people self-categorise as belonging to certain groups (e.g., as members of a national, gender, family, occupational, community, or sports group), they tend to adopt the norms, values, and attitudes of those groups as their own. The stronger their social identification with a group and its members, the more likely it is that they will behave in ways that reflect the beliefs and values of that group [31]. Put simply, it is this sense of identification that gives social groups the power to influence a person’s thoughts, feelings, and behaviour [32]. Furthermore, depending on the group’s norms and values, this influence can be positive (e.g., leading to the provision of support) or negative (e.g., leading to discriminatory behaviour).

Most relevant to the present protocol is the social identity approach to health and well-being, which has become known as the *social cure* approach [33, 34]. According to the social cure approach, groups that we identify with provide us with access to a range of psychological resources — such as social support, an enhanced sense of control, a sense of belonging, self-esteem, and emotion regulation [35–37]. These in turn help people to cope and manage the many challenges they face in health contexts. The more positive group memberships a person has, the more resources they can draw upon as they need. In line with these claims, emerging evidence from social prescribing research in the UK indicates that an increase in the number of groups that people belong to leads to better health-related quality of life [38] and improved health service usage [23]. Moreover, these effects appear to be in line with predictions from the social identity approach, with reductions in loneliness flowing from an increased sense of community belonging and social support.

Research interrogating the social cure approach has contributed to development of the social identity model of identity change (SIMIC) [34, 39], which specifies the group processes that support health and well-being in the context of life change (e.g., transitions to university study, parenthood, recovery from illness). This model argues that life transitions typically entail a loss of social group memberships and related social identities, and that, other things being equal, this will tend to compromise wellbeing. At the same time, though, SIMIC argues that in the context of life transitions, multiple group memberships and associated identities are generally protective of health and wellbeing. This is because having access to multiple group memberships (a) increases people’s ability to maintain some of these in the context of the transition (and thereby have a sense of social identity continuity) and (b) provides them with a platform for developing new group memberships (and thereby have a sense of social identity gain) and should thereby increase people’s access to health-supporting psychosocial resources. This should be more true to the extent that different group memberships are compatible as this makes them easier to manage and less stressful [40, 41].

The social identity approach argues that a lack or loss of group memberships is a significant determinant of loneliness [42]. Moreover, this lack of group memberships is often a particular problem for people who experience economic disadvantage, disability, or chronic health problems [3]. SIMIC suggests that here loneliness can result from the fact that those who are marginalised in this way may have limited existing group memberships and identities and therefore few, if any, psychosocial resources to draw upon in stressful times. Here, we are considering the lonely person’s referral to a social prescribing program to be a transitional period whereby they develop a relationship with a link worker and become engaged in a meaningful group activity. The model predicts that, to the extent that the person identifies with their new group, they will be able to access group-based psychosocial resources. Two psychosocial resources that appear most relevant to the experience of loneliness are social support given and received, and emotional sharing with other members of the group. Support given and received have been shown in previous research to mediate the relationship between group identification and (lower) stress and life satisfaction [43]. Group-based emotion regulation is predicted to decrease individuals’ experience of loneliness — itself a negative emotional state [1]. Indeed, research suggests that emotion regulation plays a key role in the dynamics of loneliness [42, 44].

Thus, the study will test the extent to which joining one or more new groups through social prescribing initiatives (2), and the associated social identity gain, provides participants with opportunities to give and receive support from others, and to regulate their own and others’ emotions (5), which are expected in turn, to decrease loneliness, decrease inappropriate health service use, and increase wellbeing (6). In addition, those individuals who are fortunate to have existing group memberships and identities before joining the social prescribing program are expected to report positive outcomes to the extent that they maintain their former groups and identities (3), and that these are compatible (4) with the new group memberships and identities gained through the social prescribing initiative.

The proposed study responds to recent calls for more research into social prescribing (e.g., in the 2021 QLD Parliamentary Inquiry into social isolation and loneliness, the 2020 Royal Australian College of General Practitioners / Consumers Health Forum Round Table report, and the 2020 Friends for Good More than Medicine report). It also addresses the need for high-quality evidence to evaluate social prescribing in an Australian context. We will evaluate the effectiveness of social prescribing, in comparison to GP treatment as usual (TAU), in reducing loneliness, as well as its effects on wellbeing and health service usage across an 8-week period.

We hypothesise that participants who participate in social prescribing will show significant improvements in loneliness and wellbeing and lower use of health services relative to those in the TAU condition. Second, the study will test the processes through which observed outcomes occur, with a focus on evaluating the two pathways in the expanded SIMIC-based model to determine whether number of important social groups, new group identification, old and new group identity compatibility, and group-based psychological resources (support given and received, and emotion regulation) are implicated in reduced loneliness and health service use and increased wellbeing over the course of the study.

## Methods

### Design and participants

While a randomised controlled design would be the strongest methodology, it requires participants to be interested and available to attend sessions with a link worker and then group activities as part of the social prescribing intervention if they are allocated to the treatment condition. It would be difficult to retain participants in social prescribing who are not interested and/or available, and conversely, it would be unethical to withhold social prescribing from participants who are interested and available, given evidence that it is potentially effective in managing loneliness. Accordingly, as shown in Fig. 2, our study will have a non-randomised controlled (parallel) design, with a social prescribing condition (SP) and a primary care treatment as usual (TAU) condition.

This research will take place in 5 sites in Southeast Queensland where social prescribing is offered, using a combination of GP and community centre models. The sites are in areas with diverse populations in terms of socioeconomic and cultural backgrounds: a community centre in a southern suburb of Brisbane, a GP clinic in the same suburb, a GP clinic in a southwestern suburb of Brisbane, a community centre in a northern suburb of Brisbane, and a combined GP and community centre in a regional city located about an hour’s drive south of Brisbane.

*Social Prescribing participants* (SP) will be adults aged 18 and over, experiencing loneliness or social isolation who are eligible for referral to the social prescribing programs at these sites. Local General Practitioners and Allied Health Professionals expected to be the most likely referral pathway. Recruitment will be promoted through the authors giving talks to referring agents and through project steering meetings. Participants will have sufficient English language skills to be able to provide consent to participate in the research. We expect them to range in age, and to represent a variety of cultural and ethnic groups. Exclusion criteria are that the individual reports acute symptoms (such as suicidal ideation, manic or agitated behaviour, or intoxication), or an acute social issue (such as domestic violence or housing crisis that would need to take priority), that would interfere with their capacity to engage with SP. Such individuals will be directed by the Link Worker to a more suitable service. Link Workers will refer clients who indicate an openness to participating the study to the researchers who will contact individuals to confirm their consent to participate in the study.

*Treatment as Usual participants* (TAU) will be selected from GP clinics in the same locations as the social prescribing programs and will meet our inclusion and exclusion criteria. A staff member within each of these services will identify frequent attending patients who will be contacted by telephone by the researchers and invited to participate in the study. Frequently attending patients will be defined as patients attending the practice 12 or more times each year over a two-year period who have not already been referred to a social prescribing scheme. These parameters remove patients attending frequently for short-lived medical needs, such as a pregnancy. We will assess for baseline differences between the conditions and statistically control for any variables that are found to differ significantly at baseline.

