### Power calculation

An a priori power analysis indicates that a sample size of 90 would be required to detect a significant difference between groups with a medium effect size (*f* = .30) on primary outcome variables, with a power of 0.8 and a default alpha of .05, using the planned 2 X 2 mixed analysis of variance. Our goal for recruitment is therefore to continue until we reach 90 with data at both time points (i.e., 45 in each condition).

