### Analysis

To assess the effect of the SP intervention, group differences on the primary and secondary outcome measures will be examined using a series of mixed-effects repeated measures (MMRM) models, which will specify timepoint, participant, and condition as levels in the analyses. MMRM is a full-information maximisation likelihood estimation strategy that can model data even when some observations are missing, and thus honours the intention-to-treat principle [50]. For all hypothesis testing, both intention-to-treat analyses (ITT; where all available data are included in MMRM) and per-protocol analyses (PP; only including participants who met eligibility criteria throughout the trial period, completed the intervention according to the protocol and had both baseline and follow up data) will be completed. Furthermore, we will test the extended Social Identity Model of Identity Change (Fig. 1) using a structural equation modelling approach that accounts for nested data (i.e., individuals within group programs) to test relationships across time between group membership, new group identification, old and new group compatibility, help given to others in the group, interpersonal emotion regulation, and the outcomes of loneliness, wellbeing, and health service use.

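### Treatment-as-usual (TAU) recruitment is not tied to social prescribing (SP) recruitment by locality and the effect model has no location term, so the SP-TAU contrast can become partly a comparison of locations

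*Protocol article*

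**What the plan says.** Under Design and participants, the Protocol article explains why the study is not randomised and places it in "5 sites in Southeast Queensland where social prescribing is offered, using a combination of GP and community centre models". The list opens with a community centre and a GP clinic in one southern suburb and continues with "a GP clinic in a southwestern suburb of Brisbane, a community centre in a northern suburb of Brisbane, and a combined GP and community centre", the last of these in a regional city. That makes five sites in four localities: southern, southwestern, northern and regional. Of the areas it says: "The sites are in areas with diverse populations in terms of socioeconomic and cultural backgrounds".

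The SP arm is drawn from people eligible for the programs at these sites. TAU participants "will be selected from GP clinics in the same locations as the social prescribing programs and will meet our inclusion and exclusion criteria". The same section promises to compare the conditions at baseline and to adjust for whatever differs significantly.

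Under Power calculation, recruitment is to "continue until we reach 90 with data at both time points (i.e., 45 in each condition"). No figure by site or locality is given. Under Analysis, the effect models are ones "which will specify timepoint, participant, and condition as levels in the analyses". The nesting of people within group programs is mentioned only for the structural equation model of process.

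**The concern.** Without randomisation, comparability depends on where and how the controls are found. SP can enter through community centres as well as clinics, whereas TAU enters through clinics only. A rule that fixes only the overall totals would be met if most SP participants came from the centres and most TAU participants from one clinic. For the northern suburb, the article lists a community centre and no GP clinic, so it does not show where that locality's controls come from.

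If the location mix differs between arms and 8-week change differs between locations (local services, economic conditions, activities on offer), the condition-by-time effect takes up part of that difference. It could create or hide an SP effect. This is confounding, not a standard-error problem, and cluster-robust errors would not remove it. If location is adjusted for only after uneven recruitment, participants in a locality with one arm add nothing to the contrast.

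**Working it through.** **Inputs from the Protocol article (Power calculation).** The sample is sized "to detect a significant difference between groups with a medium effect size", f = .30, "with a power of 0.8 and a default alpha of .05", with 90 completers, 45 per condition. For two equal groups, d = 2f = 0.60. Sidedness is not stated; two-sided is assumed.

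**Reproducing the plan's figure.** A two-group F test with noncentrality N·f² gives power 0.795 at N = 88 and 0.804 at N = 90. The stated 90 is reproduced.

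**Assumed inputs.** The article gives no per-site counts and no location effects, so the splits and effects below are illustrations. Counts are in the order southern / southwestern / northern / regional.

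**1. Power of a within-location contrast.** Information I = Σ n_SP·n_TAU/(n_SP + n_TAU) over localities. Power comes from a noncentral t with noncentrality 0.60·√I.

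| Split (SP against TAU) | Terms | I | Share of 22.5 | Power |
|---|---|---|---|---|
| Matched, 18/9/9/9 in both arms | 9 + 4.5 + 4.5 + 4.5 | 22.5 | 100% | 0.80 |
| 18/9/9/9 against 11.25 in each locality | 6.92 + 5 + 5 + 5 | 21.92 | 97% | 0.79 |
| 18/9/9/9 against 15/15/0/15 | 8.18 + 5.63 + 0 + 5.63 | 19.43 | 86% | 0.74 |
| 18/3/15/9 against 15/15/0/15 | 8.18 + 2.5 + 0 + 5.63 | 16.31 | 72% | 0.67 |

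The loss is appreciable only in the last two rows, where the northern suburb has SP participants and no TAU participants.

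**2. Bias without location adjustment.** Bias = (difference in location mix between arms) × (difference in 8-week change between those locations). The ranges assumed are 20 to 40 points and 0.25 to 0.5 SD. Results are for 45 per arm.

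| Bias (SD) | Type I error | Power if the bias runs against SP |
|---|---|---|
| 0.2 × 0.25 = 0.05 | 5.6% | 0.73 |
| 0.2 × 0.5 or 0.4 × 0.25 = 0.10 | 7.6% | 0.65 |
| 0.4 × 0.5 = 0.20 | 15.5% | 0.47 |

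**3. Would the baseline-difference rule catch it?** Suppose location were among the variables checked, with a chi-square test on 3 degrees of freedom.

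- 18/9/9/9 against 15/15/0/15: χ² = 12.3, p = 0.007. The rule acts.
- 18/3/15/9 against 15/15/0/15: χ² = 24.8, p < 0.0001. The rule acts.
- 9/9/18/9 against 18/9/9/9, a 20-point shift from south to north: χ² = 6.0, p = 0.11. The rule does not act, and the bias of 0.05 to 0.10 SD from step 2 stays.

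Where the rule does act, a location main effect adjusts outcome levels only. Removing location differences in 8-week change needs location-by-time.

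**The case against.** **The text already asks for the same locations.** A reader might infer that the SP-TAU contrast is in fact a comparison of locations, or that the northern suburb has no controls. The documents do not support either. The sentence on TAU commits to GP clinics in the programs' localities and does not confine them to the listed sites, so an unlisted northern clinic would comply. What remains is that the commitment governs where controls come from, not how many come from each place.

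**There is a safeguard.** The baseline-difference rule would act in both power scenarios and in a 40-point imbalance, if location is checked. That stands, and it means the worst unadjusted figures (0.20 SD, 15.5%) should not be read as the likely outcome. But location is not named, a 20-point imbalance can pass, and a main effect leaves differences in change.

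**Location effects on change may be small.** Stable level differences cancel in the condition-by-time effect, the Discussion expects little change under TAU, and GPs and allied health staff are expected to be the main route into SP even at the centres. This is fair. An effect of 0.5 SD would be close to the whole design effect of 0.60.

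**The power loss depends on the test.** For the 2 × 2 interaction at f = .30 under the usual repeated-measures convention, N = 90 gives power of at least 0.98, and the heaviest loss above (equivalent to about 65 participants) still leaves at least 0.92 for any non-negative correlation. The drop below 0.80 therefore holds only for the two-group test that reproduces the plan's 90.

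**Clinic names and site covariates are commonly left to fuller documents.** Their absence from an article is no fault, and they may stand in the full protocol or analysis plan. The point rests on what the article does fix: balance overall only, adjustment triggered by significance, and a model with three named levels.

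**Conclusion.** The point holds as a cheap improvement, not as a demonstrated flaw in the comparison. The stated recruitment rule and model leave location as an uncontrolled risk in a non-randomised study, and the significance-triggered rule is a weak guard at 45 per arm. The size of the risk cannot be derived from the article. In the illustrations it runs from nothing (arms matched by locality, power 0.80) to power of about 0.74 to 0.67 for a within-location contrast with no northern TAU, or an unadjusted bias of 0.05 to 0.20 SD with type I error of 5.6% to 15.5%. All of these rest on assumed site splits, and the bias figures also on assumed location differences in change. The stated sample size of 90 is not in question. A difference in recruitment route (frequent attenders against referred clients) is a separate comparability issue that this change would not settle.

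**What to change.** **Design and participants, and Power calculation:** keep the total of 90, but recruit TAU in step with SP within each of the four localities. State which GP clinic supplies TAU for the northern suburb.

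**Analysis:** prespecify location and location-by-time as fixed effects in the effect models, whether or not location differs significantly at baseline. Keep every participant in the intention-to-treat analysis. If a locality ends with no TAU, add a sensitivity analysis restricted to localities with both conditions, so that readers can see which data carry the contrast.

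**Cost:** no added participants. With four localities, the model spends three location terms and three location-by-time terms. TAU recruitment may be slower because it is paced to SP, and an agreement with one northern clinic may be needed. Pacing has to be settled before recruitment closes: after that, imbalance can be adjusted for only at the price of information, and an empty locality cannot be filled.
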